### Endpoints

The primary endpoint is the presence of parastomal hernia as detected by clinical examination or CT scan at 12 months after surgery. A bulge in the vicinity of the stoma is not sufficient in this study to define a parastomal hernia. If there is any doubt in the clinical setting, the patients must be examined by a CT scan in a prone position. Secondary endpoints include: re-admission rate, postoperative complications (classified according to Clavien-Dindo [27]), stoma-related complications (registered in the case record form (CRF) at Stoma Care nurse follow-up), total length of hospital stay during 12 months, health-related quality of life and health economic analysis, re-operation rate, mortality within 30 days and 12 months of primary surgery. Re-admissions and re-operations as registered in the hospitals’ databases at 24 months to ascertain that possible long-term complications related to the stoma construction are identified.

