### Statistical analysis

The Swedish trial on the effect of prophylactic net placement has reported 50% incidence of parastomal hernia without mesh [14]. Our own data on abdominoperineal excision from Sahlgrenska University Hospital indicate an incidence of 25% [28]. The power calculation based on available information has used the hypothesis that the cruciate incisional stoma formation, performed as described here, should result in parastomal hernia incidence of 30% and the circular incision or prophylactic mesh reinforcement could reduce this incidence to 10% each. An 80% power and a 5% level of significance with a two-sided alternative hypothesis would require 62 patients per group using a chi-square test. Expecting 20% drop-outs, 80 patients will be recruited in each group.

The primary analysis will be based on the full analysis set. This analysis set is designed to be consistent with recommendations set forth in International Conference on Harmonisation (ICH) guidance document E9: Statistical Principles for Clinical Trials, and is intended to adhere as closely as practically possible to the intention-to-treat (ITT) principle. The full analysis set will consist of all randomised patients who had surgery and who contributed with any follow-up data.

Patients will be analysed according to randomised procedure. A sensitivity analysis evaluating the actual procedure will be made for the most important outcomes.

All hypothesis testing will be conducted using two-sided tests, and P values ≤ 0.05 after rounding will be considered statistically significant. A pair-wise comparison between the experimental arms and the control arm will be performed and the significance level will be corrected using the Bonferroni-Holm method. Event-type variables (yes or no) will be compared between randomised procedures using chi-square tests, and relative risks and risk differences will be estimated. Where appropriate, the time to event will be described using Kaplan-Meier plots. The number of events of a certain type (for example, number of complications or re-operations) will be analysed using Poisson regression with randomised procedure as a factor and time under observation as an offset variable.

Total length of hospital stay will be compared between groups using Wilcoxon’s rank-sum test. Sub-group analyses specifically looking at the following groups of patients will be performed:

a) BMI >30 kg/m2

b) Immunosuppression

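### The rank-sum test of 12-month hospital days makes no allowance for death, so an early death can count as a short, favourable stay (secondary endpoint; effect probably small)

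*Protocol article*

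**What the plan says.** The Endpoints section lists "total length of hospital stay during 12 months" among the secondary endpoints, together with "mortality within 30 days and 12 months of primary surgery". The Statistical analysis section then gives one sentence on how stay is analysed: "Total length of hospital stay will be compared between groups using" Wilcoxon's rank-sum test.

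Just before it, numbers of events such as complications and re-operations are assigned to "Poisson regression with randomised procedure as a factor and time under observation as an offset variable". Unequal follow-up is thus recognised for counts, but nothing comparable is stated for hospital days.

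The full analysis set comprises "all randomised patients who had surgery and who contributed with any follow-up data". It is named for the primary analysis. Applying it to hospital stay is a natural reading, but the article does not say so. The sensitivity analyses concern the procedure actually performed and centres that allocated both treatments being compared. Neither deals with death.

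**The concern.** Hospital days can accumulate only while the patient is alive. A patient who dies on day 6 contributes at most 6 days, and a rank-sum test in which fewer days is better places that patient near the favourable end. Someone who survives the year with one re-admission ranks worse.

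Deaths within the window are foreseeable. Mortality is an endpoint, colorectal cancer patients are among those enrolled (Follow-up section), and the eligibility criteria set no limit on disease stage or life expectancy. If one arm had more early deaths, its hospital stay would look somewhat shorter for that reason alone. At stake is the reading of one secondary endpoint, which is meant to reflect the burden of each technique on the patient and the hospital.

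**Working it through.** **Plan's own figure.** The article states no effect size, distribution or power for hospital stay, so there is nothing to reproduce on this point. (The primary-endpoint figure of 62 per group for 30% against 10% does reproduce, but has no bearing here.)

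**Scale.** Let θ be the probability that a random patient in the higher-mortality arm has more hospital days than a random patient in the other arm, ties counted as one half. With equal underlying hospital use θ = 0.50. Below 0.50, the arm with more deaths looks better.

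**Bound.** Let d1 and d0 be the proportions dying in the two arms, and suppose every death ranks below every survivor, with deaths tied with one another. Adding the four pairings:

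θ = ½·d1·d0 + 0·d1(1−d0) + 1·(1−d1)d0 + ½(1−d1)(1−d0) = 0.5 − (d1−d0)/2.

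Each percentage point of excess mortality therefore moves θ by at most half a point. For 15% against 5%: 0.5 − 0.10/2 = 0.45. If deaths are instead ranked worst, the sign flips: 0.5 + 0.10/2 = 0.55.

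**Illustration.** All inputs here are assumptions except the 80 patients per arm. First stay: median 10 days, log-normal with log-SD 0.5. Re-admissions: on average 0.6 per patient over the year. Re-admission stay: median 6 days, log-SD 0.7. Hospital use is the same in both arms, and days stop at death. Deaths fall uniformly either within 30 days or across 12 months. There were 3,000 runs per scenario.

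| Mortality (lower vs higher arm) | Timing of deaths | θ, as planned | θ, deaths ranked worst |
|---|---|---|---|
| 5% vs 10% | within 30 days | 0.489 | 0.525 |
| 5% vs 15% | within 30 days | 0.477 | 0.550 |
| 5% vs 20% | within 30 days | 0.467 | 0.574 |
| 5% vs 10% | over 12 months | 0.496 | 0.526 |
| 5% vs 15% | over 12 months | 0.492 | 0.551 |
| 5% vs 20% | over 12 months | 0.488 | 0.574 |

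The last column agrees with the formula (0.525, 0.550, 0.575). The planned analysis falls well short of the bound. At 5% against 15% it moves θ by 0.50 − 0.477 = 0.023 with early deaths and by 0.50 − 0.492 = 0.008 with deaths spread over the year, against a maximum of 0.05.

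**Test behaviour.** With 5% against 20%, all within 30 days, the planned test rejected in 10.3% of runs, and 9.9 of those points favoured the arm with more deaths. With the same mortality spread over the year it rejected in 5.3%. With equal mortality of 5%, rejection stayed near the nominal 5% (5.3% to 6.3%).

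**Second illustration.** Assumptions: median first stay 12 days, 30% re-admitted, deaths spread over 300 days. Total stay gave 0.503 (5% vs 10%) and 0.507 (5% vs 15%) in favour of the arm with more deaths, that is θ = 1 − 0.503 = 0.497 and 1 − 0.507 = 0.493. Days alive and out of hospital gave 0.526 and 0.549 in favour of the arm with fewer deaths.

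**The case against.** The strongest reply is that this is a journal article. A rule for deaths in one secondary endpoint may stand in a full protocol or analysis plan that is not shown, and a sentence naming a test does not forbid one. That is fair as a caution. But the article does fix the window and the test, and it states an allowance for observation time for one outcome type and not for the next. A plain rank-sum test has no place for an offset.

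It is also fair that a bias between arms requires mortality to differ by arm. Patients are randomised in theatre just before the stoma is formed, to techniques that differ in fascial incision or mesh, and the article gives no reason to expect a gap of 5 to 15 points. A death after a long terminal admission would not rank as short. Mortality, complications, re-admissions and re-operations are reported separately, so a marked imbalance in deaths would be visible. All of this stands and limits the size of the point.

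Three stronger readings are tempting, and the document does not support them.

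- **Drop-out shortens the totals as well.** A reader might infer this from "Expecting 20% drop-outs, 80 patients will be recruited in each group". That figure is a sample-size allowance for the hernia endpoint, which needs an examination or CT at 12 months. The Endpoints section takes re-admissions from hospital databases at 24 months, which does not depend on visit attendance. The article does not name the source of hospital days, so this is worth settling, but it does not say that one patient in five lacks them.
- **The health economic result is distorted.** The Health economic evaluation section describes a model built on case record form and registry data with sensitivity calculations. It does not say that the rank-sum comparison feeds that model.
- **The figures near 0.55 measure the bias in hospital days.** They do not. They show the assumed mortality difference entering a composite. The bias in hospital days is the distance of the planned θ from 0.50.

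**Conclusion.** The point holds as a modest one. As written, the comparison of 12-month hospital days takes no account of death, so an early death can rank as a favourable outcome. In the unequal-mortality scenarios examined, the direction always favoured the arm with more deaths. The displacement was small: θ between 0.488 and 0.497 when deaths were spread over the year, and down to 0.467 in the extreme case of 5% against 20% mortality, all within 30 days. With equal mortality there is no systematic advantage to either arm.

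These sizes rest on assumed mortality and assumed stay distributions, since the article gives neither, and on reading the full analysis set as applying to this endpoint. The primary endpoint, its analysis and the sample size are unaffected. This is an inexpensive improvement to a secondary endpoint, not a flaw that threatens the trial's main conclusion.

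**What to change.** Keep total hospital days during 12 months with its rank-sum test, and add:

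1. A supplementary comparison of days alive and out of hospital within 365 days of surgery, in which every day after death counts as zero, using the same rank test.
2. A display of deaths and of total hospital days by arm beside both comparisons.
3. A statement that admission days are taken from the hospital databases for all patients, whether or not they attend visits.

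The cost is a few sentences on one secondary endpoint. Dates of death, admission and discharge are already needed for the mortality, re-admission and hospital-stay endpoints. The downside is that the added measure mixes survival with hospital use, so a difference on it cannot be interpreted without its two components. That is why item 2 is part of the change and why total hospital days should be supplemented rather than replaced.

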### Participating hospitals

The study will recruit patients from hospitals in Denmark and Sweden.

### Approvals and registration

The trial has been approved by the Swedish Ethical Committee (EPN/Göteborg Dnr 547-12) and the Swedish radiotherapy protection committee (Dnr 12-38). It has been approved by the Danish ethics committee (Protocol H-4-2013-061), and by the Danish Data Protection Agency (no. HEH-2013-049, I-Suite no:02418). The study was registered at http://www.clinicaltrials.gov (NCT NCT01694238) prior to inclusion of the first patient.

## Discussion

Parastomal hernia is a common complication after stoma creation (12, 13). There are several randomised trials that have tried to evaluate a reduction of the occurence of parastomal hernia with placement of a prophylactic mesh [13,14,30]. However, the use of a prophylactic measure must be evaluated in relation to health-related QoL as well as health economy. It is important to have enough power to thoroughly evaluate possible complications and side effects. A recent health technology assessment at Sahlgrenska University Hospital concluded that mesh probably is beneficial in regard to parastomal hernia formation, but that further studies are required [31]. At present there are at least six other randomised trials investigating the importance of a mesh for prevention of parastomal hernia, including one Norweigan study [32] with 60 patients, one Danish study that was stopped before including the planned 198 patients [33] and one Swedish study with 300 patients [34]. Sixty patients are randomised to mesh/no mesh in a Spanish study [35], another Spanish study is randomising 32 patients to intraperitoneal mesh placement [36] and 200 patients are randomised in a French study [37]. In addition there is a Dutch study, with 150 patients [38].

Our study will provide additional information complementing these studies through the evaluation of the surgical technique without a mesh in the control arm and in the interventional arms. Furthermore, the QoL and health economic evaluation will enable improved decision-making regarding prophylactic measures against parastomal herniation.

## Trial status

The trial is ongoing and recruiting patients at centres in both Denmark and Sweden. Hospitals interested in participating are welcome to contact the corresponding author.

## Abbreviations

ASA classification: American Society of Anaesthesiology classification; BMI: body mass index; CRF: case record form; CT: computed tomography; EPN: Ethical committee; ICH: International Conference on Harmonisation; ID: identification; IT: information technology; ITT: intention to treat; QoL: quality of life.
